### Analysis plan

Statistical analysis will be guided by the conceptual frameworks presented for each of the study outcomes (Figures 2, 3, 4 and 5). The analysis of the primary study outcomes will use multiple logistic regression to estimate the Odds Ratios for exposure-outcome associations with adjustment for appropriate confounding factors. For example, *a priori *confounders for the association between maternal geohelminth infections and eczema by 3 years of age are gender, maternal educational level, household crowding, and infant geohelminth infections. The primary analyses will evaluate the effects of maternal geohelminth infections or infant geohelminth infections on: 1) protective immunity to common childhood vaccines: 2) the presence of allergen skin test reactivity at 5 years of age; 3) the development of eczema by 3 years of age; and 4) the development of asthma at 5 and 8 years of age. Immunological variables will be defined as binary variables with a cut-off defined by the limit of detection of the assays (i.e. IL-10) or median level (i.e. IL-8) or as log_e_-transformed continuous variables. Because immunological variables are considered as intermediate in the causal pathways between exposures and outcomes, these variables will be evaluated in hierarchical analyses [60].

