### Study population and area

The Province is one of the poorest regions of Ecuador, with a per capita income of less than US$2,000 in 2005. Quinindé is a rural District that covers an area of 3,471 km^2 ^and includes 1 urban (the town of Quinindé) and 6 rural parishes with an estimated population of 150,000. The District is located in an area of (formerly) equatorial rainforest that has largely been cleared, at an altitude of approximately 100 m and average annual day temperature of 30°C and 75% humidity. The District has an ethnically mixed population of mestizos (90%), Afro-Ecuadorians (7%), and Amerindians (3%). Twenty-two percent of the population is estimated to be urban (Quinindé town) and 78% rural. In the town of Quinindé, approximately 90% of the population have access to electricity, 60% to treated drinking water, 40% to sanitation; 60% to solid waste disposal services. In contrast, in the rural areas, 10% have access to electricity and none have access to other services. The main sources of income are derived from African palm oil and fruit cultivation, cattle, and extraction of timber. The study is based at the Hospital "Padre Alberto Buffoni" (HPAB) (H in Figure 1) in Quinindé town. HPAB is the only Hospital serving the District and the only health centre with maternity services.

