### Sampling and evaluations

The sampling and examination schedule for follow-up is shown in Table 1. Evaluations are conducted at birth, 2 weeks, 3, 7, 13, 18, 24 and 30 months, and at 3, 5, and 8 years through home visits and scheduled visits at the ECUAVIDA outpatient clinic at HPAB. More detailed immunologic evaluations are performed in an immunology sub-cohort (ISC) of the last 295 infants recruited using blood samples collected at birth, 7, 13 and 24 months, and at 3, 5 and 8 years. A surveillance sub-cohort of 195 newborns living within the town of Quinindé are being followed-up actively and sampled for viral respiratory tract infections (influenza viruses, respiratory syncytial viruses, adenoviruses, and rhinoviruses) using nasal swabs and diarrheal illnesses (rotavirus and norovirus) using stool samples during the first 2 years of life. Aliquots of all stool samples collected and hypopharyngeal swabs (at routine sampling times) are being stored for future analyses of bacterial microbiota.

**Table 1 T1:** Sampling schedule for ECUAVIDA cohort

Visit	Ante-natal	Birth	< 2 wks	3 mths	7 mths	13 mths	24 mths	3 years	5 yrs	8 yrs
**Site**	**HPAB**	**HPAB**	**Home**	**HPAB/home**	**HPAB/home**	**Home**	**HPAB/home**	**HPAB/home**	**HPAB/home**	**Home**

Child										
Questionnaire		X	X		X	X	X	X	X	X
Faeces		X	X	X	X	X	X	X	X	X
Blood		X^a^	X		X	X	X	X	X	X
Clinical exam		X	X		X	X	X	X	X	X
Anthropometry		X			X		X	X	X	X
SPT							X	X	X	X
PFTs/BHR										X
Mantoux test										X

Mother										
Questionnaire	X	X	X	X						
Faeces	X	X	X							
Blood	X									
SPT										

Father										
Faeces			X	X						
SPT										

Household										
GPS			X^b^			X^b^				
Dust			X^b^							
Faeces			X							

Stool samples are collected also at 18 and 30 months. HPAB-Hospital Padre Alberto Buffoni in Quinindé, Esmeraldas Province; SPT-allergen skin test reactivity; PFTs-pulmonary function tests measured by spirometry; BHR-bronchial hyperresponsiveness or evidence of reversibility following β_2 _agonist; GPS-geographic positioning system measurements for mapping of households. ^a ^immunology sub-cohort only. ^b ^measurements repeated for change of address.

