### Study limitations

We expect losses to follow-up to be up to 10% in the first year (i.e. 2,163/2,403 followed up) and 5% annually to age 3 and a further 5% between ages 3 and 5. Estimates for the number of children followed-up are: 2 years-2,055, 3 years-1,952, and 5 years-1,854. Losses are due to the mobility of the study population.

Potential sources of biases are selection bias caused by losses to follow up and information bias caused by systematic misclassification of outcomes. The following methods are being used to minimize these biases: *Achieving high rates of follow-up *- a) we have a well-trained study team employed full-time for the cohort; b) we conduct regular home visits to maintain contact with study mothers; c) the universal use of mobile phones allows us to maintain regular contact with study mothers; d) the mother of each child is given a cohort identification card with a phone number to make appointments at the ECUAVIDA outpatient Clinic; e) changes of address are followed up actively with home visits to repeat environmental sampling. *Information bias *- a) repeated measurements of outcomes (for asthma, eczema, and allergen skin test reactivity) should reduce misclassification and recall bias; b) clear definitions for primary outcomes and exposures; c) evaluation of outcomes is being performed blind to exposure status. Detailed information on potential confounding factors is being collected.

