### Study power

The study sample size is fixed at 2,403 newborns. Primary outcome variables will be treated as statistically independent. Power calculations for primary study questions are shown in Table 2[58,59]. We expect a high degree of power for the estimation of most primary and secondary study outcomes (≥ 80% depending on immunological mechanism at α = 0.01) that will allow for the loss of power expected by controlling for confounding.

**Table 2 T2:** Power for analysis of primary exposure-outcome associations

Primary exposures (geohelminth infections)	Outcome	Sample size available	Analysis sample size	Exposure prevalence	Expected prevalence of outcomes (exposed vs. unexposed groups)	Α	Power
Maternal	Vaccine antibodies @ 7 mths						
	Hib	2,300	1,000	50%	65% vs. 75%	0.01	80%
	Rotavirus	2,300	1,000	50%	40% vs. 60%	0.01	> 99%
Maternal	Vaccine antibodies @ 2 yrs						
	TT	1,955	1,000	50%	85% vs. 95%	0.01	> 99%
	HBV	1,955	1,750	50%	80% vs. 85%	0.05	80%
	OPV type 3	1,955	500	50%	80% vs. 95%	0.01	> 99%
Infant	Vaccine antibodies @ 5 yrs						
	TT	1,725	1,000	35%	60% vs. 80%	0.01	99%
	HBV	1,725	1,500	35%	70% vs. 80%	0.01	95%
	OPV type 3	1,725	1,000	35%	50% vs. 70%	0.01	> 99%

Maternal	SPT @ 3 years	1,840	1,840	50%	15% vs. 25%	0.01	99%
Infant	SPT @ 3 years	1,840	1,840	35%	15% vs. 25%	0.01	> 99%

Maternal	Eczema @ 3 years	1,840	1,840	50%	25% vs. 35%	0.01	99%

Maternal	Asthma @ 5 years	1,725	1,725	50%	17% vs. 23% #	0.05	86%
Infant	Asthma @ 5 years	1,725	1,725	35%	17% vs. 23% #	0.05	83%
Infant	Asthma @ 5 years	1,725	1,207	20%	25% vs. 15% #	0.01	93%

Random samples of the study population will be selected for analysis of the protective levels of vaccine antibodies. Based on data from the cohort we estimate that 20% of children will have allergen skin test reactivity to any allergen at 5 years, that 30% of children will have at least one documented episode of eczema by 3 years of age and that 20% of children will have asthma at 5 years. Based on data from the cohort we estimate that ~50% of mothers are infected with any geohelminth parasite and ~30% of children will have at least one documented geohelminth infection during the first 2 years of life.

#-expected effects of geohelminth infections on asthma prevalence using data from cross-sectional analyses in Ecuador [58] and Brazil [59].

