### Potential effects of geohelminth infections on the development of allergic inflammatory diseases

*Asthma *is a heterogeneous disease caused by complex interactions between host genetics and environment. Rural residence appears to be strongly protective against the development of allergic disease that may be mediated by common exposures present in the rural environment [102], particularly in early life [90]. Early infections are considered to be particularly relevant [92,103-107]. Geohelminth infections in childhood are inversely associated with asthma symptoms [34] or specifically asthma associated with atopy [87] in some populations that are highly endemic for these parasites. The effects of different geohelminths parasites on asthma may be distinct [34]. However, there is also growing literature that points to a role of helminths, particularly *A. lumbricoides*, as a risk factor for asthma in populations with a low prevalence of infection [108-114].

Atopy has been consistently linked to asthma in developed countries but there is evidence that the association between asthma and atopy in developing countries is weaker [87,98,115-117]. An explanation for this observation is that is that the more prevalent infectious exposures including geohelminth infections present in many developing countries may attenuate the association through a reduction in allergic sensitization.

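### The confounder set stated for the maternal-infection/eczema model omits urban/rural residence and sanitation, which the article's own text makes plausible common causes of infection and of less allergy

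*Protocol article*

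**What the plan says.** The Analysis plan section commits the primary outcomes to multiple logistic regression "with adjustment for appropriate confounding factors". It then gives one worked case, stating that the a priori "confounders for the association between maternal geohelminth infections and eczema by 3 years of age are gender, maternal educational level, household crowding", with infant infection as the fourth and last. The case is introduced as an example, but the list for that model is worded as the set itself, not as a selection from it.

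Elsewhere the article says four things that bear on this list:

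- Study population and area: the District is 22% urban and 78% rural. In the town about 60% have treated water and 40% sanitation, whereas "in the rural areas, 10% have access to electricity and none have access to other services".
- Discussion, allergic inflammatory diseases: "Rural residence appears to be strongly protective against the development of allergic disease". The article adds that this may act through shared exposures in the rural environment, particularly early in life.
- Discussion, allergic sensitization: detectable spontaneous IL-10 has been linked to poor sanitation. The eczema paragraph names raised spontaneous IL-10 as a route by which maternal infection might protect.
- Table 1 schedules household location for the cohort: "GPS-geographic positioning system measurements for mapping of households".

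The Study limitations section adds: "Detailed information on potential confounding factors is being collected". It does not name the factors.

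**The concern.** The hypothesis is that maternal infection in pregnancy protects the child from eczema. The parasites are soil-transmitted, so a household without sanitation is a plausible cause of maternal infection. On the article's own account, rural living, and the IL-10 profile that goes with poor sanitation, are plausible causes of less allergy. Residence and sanitation would then be common causes of exposure and outcome. A model that leaves them out tests for association given the four listed terms, and that association can arise with no effect of maternal infection at all.

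The expected bias is towards protection, the direction hypothesised. The Background section ties the findings to the debate on anthelmintic treatment in pregnancy, so a protective odds ratio explained partly by where the family lives could mislead that debate.

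**Working it through.** **1. The plan's own figure.** The "Eczema @ 3 years" row of Table 2 has 1,840 children, 50% exposed (920 per group), 25% vs 35%, alpha 0.01 and power 99%. For the pooled two-proportion test, two-sided:

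- SE under the null = sqrt(2 × 0.30 × 0.70 / 920) = 0.02137
- SE under the alternative = sqrt((0.25 × 0.75 + 0.35 × 0.65) / 920) = 0.02124
- Power = Φ((0.10 − 2.576 × 0.02137) / 0.02124) = Φ(2.12) = 98.3%

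One-sided it is 99.1%. The stated power reproduces. The planned odds ratio is (0.25/0.75) / (0.35/0.65) = 0.62. The power figure is not in question here; the validity of the contrast is.

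**2. Inputs for the confounding check.** From the article: N = 1,840, 50% of mothers infected, 30% eczema by 3 years, 78% rural (District figure). Assumed, because the article does not give them: maternal infection in urban households of 20%, 30% or 40%, and urban eczema of 35%, 40% or 45%. The true effect of maternal infection is set to zero, and residence is the only common cause.

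**3. Formulas.** With i for infection, e for eczema, and subscripts U (urban) and R (rural):

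- i_R = (0.50 − 0.22 i_U) / 0.78 and e_R = (0.30 − 0.22 e_U) / 0.78
- P(rural | infected) = 0.78 i_R / 0.50; P(rural | uninfected) = 0.78 (1 − i_R) / 0.50
- Eczema in each infection group = P(rural) × e_R + (1 − P(rural)) × e_U
- Rejection probability: the two-sided form of the test in step 1

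**4. One setting in full** (i_U = 30%, e_U = 40%):

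- i_R = 0.434 / 0.78 = 0.556; e_R = 0.212 / 0.78 = 0.272
- P(rural | infected) = 0.868; P(rural | uninfected) = 0.692
- Eczema, infected: 0.868 × 0.272 + 0.132 × 0.40 = 0.289
- Eczema, uninfected: 0.692 × 0.272 + 0.308 × 0.40 = 0.311
- Spurious odds ratio = (0.289/0.711) / (0.311/0.689) = 0.90
- Rejection at 0.01 = Φ((0.0226 − 2.576 × 0.02137) / 0.02136) = Φ(−1.52) = 6.4%; the opposite tail is negligible

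**5. All nine settings**, residence not adjusted:

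| Urban / rural infection | Urban / rural eczema | Spurious OR | Rejection at 0.01 |
|---|---|---|---|
| 20% / 58% | 35% / 29% | 0.92 | 3.8% |
| 20% / 58% | 40% / 27% | 0.85 | 16% |
| 20% / 58% | 45% / 26% | 0.785 | 42% |
| 30% / 56% | 35% / 29% | 0.95 | 2.1% |
| 30% / 56% | 40% / 27% | 0.90 | 6.4% |
| 30% / 56% | 45% / 26% | 0.85 | 16% |
| 40% / 53% | 35% / 29% | 0.97 | 1.3% |
| 40% / 53% | 40% / 27% | 0.95 | 2.1% |
| 40% / 53% | 45% / 26% | 0.92 | 3.8% |

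**6. With residence in the model.** Within each stratum of residence the odds ratio is 1 by construction, so rejection returns to the nominal 1%. In simulation (600 cohorts per setting) it was 0.3% to 1.7%.

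**7. Sensitivity to the rural share.** The cohort's own split is not given. With a rural/urban odds ratio of 2 for infection and 0.5 for eczema, rejection is 4.2% at 78% rural and 7.7% at 50% rural. With 3 and 0.5 it is 10% and 22%.

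**The case against.** The strongest reply is that this is one example in a condensed article. The text promises adjustment for appropriate confounders and says detailed confounder data are being collected. It ties the analysis to conceptual figures, of which Figure 5 (eczema) cannot be seen, and a separate analysis plan may list more. That stands as a caution: a reader might infer that residence is ruled out of the final model, and the article does not say so. It does not remove the point, because the set that is published for this model lacks both variables and the general statements name neither.

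Second, the check uses a crude model. A reader might take 1% to 42% as the false-positive rate of the planned model; it is not. Education, crowding and infant infection could all act as proxies for the household environment, and the bias left after adjusting for them is unknown. This stands.

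Third, both driving contrasts are assumed. The article nowhere reports maternal infection by residence, and 60% of the town also lacks sanitation. The rural-protection sentence concerns allergic disease in general and sits in the asthma paragraph, while the eczema paragraph says little is known of environmental risk factors in the tropics. Part of the rural protection might itself run through helminths, whereas the check assigns all of it to other causes. The largest rates need strong inputs: urban infection of 20% implies a rural/urban odds ratio of about 5.6, and at 40% (about 1.7) rejection is only 1.3% to 3.8%. All of this stands and limits the size that can be claimed.

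Three further criticisms are tempting but unsupported. Gender cannot cause maternal infection, but adjusting for it does no harm, and the case for removing it or infant infection is not made. The article lists no confounders for skin tests, asthma or vaccines, so there is no stated set to correct there. Not using the fathers' stool samples as a negative control is not an error.

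**Conclusion.** The point holds for the one model whose adjustment set is stated. The list leaves out residence and sanitation, which the article's own statements make plausible common causes of maternal infection and of less allergy. The inflation depends on contrasts that the article does not give. It is negligible at the weak end of the assumed range and serious at the strong end. The range is neither an estimate for the planned analysis nor a hard limit, since a different rural share would move it.

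A reader might go further and infer that residence alone could manufacture the effect the study is powered for. The nine settings do not support that: the most extreme spurious odds ratio is 0.785, against 0.62 planned. Confounding of this kind could produce a significant result, or exaggerate a true one, without matching the planned effect in full.

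**What to change.** In the stated adjustment set for maternal infection and eczema, add urban/rural residence, derived from the recorded household address or GPS position. Where collected, also add household sanitation and water access. Keep the four terms already listed. Report the maternal-infection odds ratio with and without the added terms, so that readers can see how much of it residence explains. If residence or sanitation is left out on purpose, state the reason.

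The cost is a change of wording, a few model terms and a small loss of precision. Residence needs no new data, because household location is already recorded. A parallel analysis of the fathers' infection, using the stool samples scheduled in Table 1, could be offered as exploratory; the fix does not depend on it.

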### Measurement and definition of geohelminth exposures

Stool samples to measure geohelminth infections have been collected from mothers in the third trimester of pregnancy (stool samples collected after birth and before the child is 14 days old are considered to represent a third trimester stool sample where the mother has not received anthelmintic treatment) and from infants at 3, 7, 13, 18, 24, and 30 months, and at 3, 5, and 8 years. Stool samples are analysed using a combination of standard methods including direct saline mounts, the modified Kato-Katz method, formol-ether concentration, and carbon-coproculture methods [45]. Geohelminth infectious exposures will be defined as follows: 1) maternal geohelminth infections-presence of any geohelminth infection detected during the 3^rd ^trimester of pregnancy; and 2) infant geohelminth infections-presence of any geohelminth infections detected during the first 2 years of life.

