**Figure 2 F2:**
[figure not shown]
**Conceptual model for effects of maternal and infant geohelminth infections on vaccine immune responses measured at 7 months, 2 years or 5 years**. Maternal infections would be expected to mediate effects on vaccine responses at 7 months and 2 years, although infant infections, generally acquired during the second year of life, may contribute to effects at 2 years. The suppressive effects of infant infections would be expected to be most important at 5 years. Potential immunological mechanisms that may mediate the suppressive effects of geohelminth exposures are shown in dashed boxes.

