*Eczema *is a chronic relapsing inflammatory skin disease that may be caused by an impaired ability to regulate inflammation induced by environmental insults in the presence of impaired skin barrier function [122]. Eczema generally develops within the first 6 months of life [123], peaks in prevalence between 2 and 3 years [124], after which the prevalence declines [125]. Little is known of the natural history of eczema in tropical environments with respect to prevalence, severity, environmental risk factors, and associations with atopy. The association between eczema and geohelminth infection is controversial [126] and studies have shown both positive [127] and negative [128-130] associations. An intervention study in Uganda provided evidence that treatment of geohelminths during pregnancy was associated with a reduced risk of eczema at 1 year [130]. Infants of infected mothers in the placebo group had a reduced prevalence of eczema compared to those of non-infected mothers [130].

The mechanisms by which geohelminth infections may reduce the risk of eczema are not known. Possible mechanisms are illustrated in Figure 5. The strongest effects are likely to be mediated by maternal infections because the disease often appears before infant geohelminth infections are acquired. The clinical presentation of eczema is a direct consequence of the damage caused by repeated scratching of the skin. Eczema, may therefore, be caused by numerous external insults that cause pruritus. A novel finding is that children born in the rural Tropics rapidly down-regulate pro-inflammatory responses to innate immune stimuli [56]. Such age-dependent responses are likely to be important adaptive mechanisms by which an early capacity to respond to innate immune stimuli that may be important in the absence of adaptive immunity but associated with an increased risk of pathologic inflammation, is rapidly down-regulated once specific adaptive immune responses have developed. We hypothesize, therefore, that the protective effects of maternal geohelminth infections are likely to be associated with markers of early immune maturation and mediated by non-specific and generalized anti-inflammatory effects (e.g. increased spontaneous IL-10) and regulation of innate (i.e. reduced IL-8 production to TLR agonists) and adaptive (i.e. elevated frequencies of induced regulatory T cells [i.e. CD4^+^IL-10^+ ^Tr1 cells]) immunity.

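### The maternal-infection eczema model adjusts for infant infection, which follows the exposure and often the eczema, so its odds ratio is not the total maternal effect and is open to bias of unknown size and direction

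*Protocol article*

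**What the plan says.** The Analysis plan section of the protocol article specifies multiple logistic regression for the primary outcomes. As its worked example it gives the a priori confounders for maternal infection and "eczema by 3 years of age are gender, maternal educational level, household crowding, and infant geohelminth infections". No other adjustment set is spelled out in the article.

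The section on measurement and definition of geohelminth exposures fixes when the two infection variables occur:

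- Exposure: "maternal geohelminth infections-presence of any geohelminth infection detected during the 3^rd ^trimester of pregnancy".
- Covariate: "infant geohelminth infections-presence of any geohelminth infections detected during the first 2 years of life".

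Two further places bear on the order of events. The Figure 2 legend describes "infant infections, generally acquired during the second year of life". The eczema discussion, under potential effects on allergic inflammatory diseases, puts usual onset within the first 6 months and expects maternal infection to have the strongest effect "because the disease often appears before infant geohelminth infections are acquired". The outcome definition counts any qualifying presentation in the first 3 years, with scheduled assessments at 7, 13, 24 and 36 months.

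The Analysis plan sends the immunological variables to hierarchical analyses because they are seen as lying on the causal pathway. Infant infection gets no such treatment in the eczema example.

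**The concern.** A confounder has to precede the exposure or stand in for something that does. Infant infection up to 24 months comes after a third-trimester exposure. It may lie on the path from maternal infection to eczema, in which case adjusting for it removes part of the effect. It may share unmeasured causes with eczema, in which case adjusting for it opens a non-causal path. Where eczema came first, the model conditions on an event later than the outcome.

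Hypothesis 3 counts infant infection as part of the chronic exposure expected to protect against eczema, so the article itself expects a link between this covariate and the outcome. A link from mother to infant is plausible but is neither stated nor quantified.

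At stake is the meaning of the primary odds ratio for eczema. Because this is the article's example of how covariates are chosen, the same choice could also be copied into other maternal models.

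**Working it through.** **1. The plan's own figure.** Table 2, eczema at 3 years: 1,840 children, 50% exposed, 25% vs 35%, alpha 0.01, power 99%.

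- Odds ratio = (0.25/0.75) / (0.35/0.65) = 0.333/0.538 = 0.62.
- With 920 per group, the standard error under no difference is √(2 × 0.30 × 0.70/920) = 0.02137, and under the alternative √((0.25 × 0.75 + 0.35 × 0.65)/920) = 0.02124.
- z = (0.10 − 2.576 × 0.02137)/0.02124 = 2.12, so two-sided power is 98.3%, within a point of the stated 99%.

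This is an unadjusted two-proportion calculation. It says nothing for or against the adjustment set.

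**2. Order of events.**

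| Variable | Timing in the article |
|---|---|
| Maternal infection | Third trimester |
| Eczema | Generally from the first 6 months; any presentation to 3 years counts |
| Infant infection | Any positive stool to 24 months; generally second year |

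The covariate follows the exposure in every child. It often follows the outcome in children who develop eczema early.

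**3. What adjustment can do.** Inputs from Table 2 and its notes: maternal infection 50%, infant infection about 30%, eczema 30%. The odds ratios linking maternal infection, infant infection, eczema and any common cause are assumptions, because the documents give none.

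*Eczema first, then infant infection.* True odds ratio 0.62. Assume a maternal–infant odds ratio of 3 and an eczema-to-later-infection odds ratio of 0.6. For infant infection to be 30% overall, its odds with neither maternal infection nor eczema must be 0.267. The odds and probabilities are then:

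- neither: 0.267, probability 0.2107
- eczema only: 0.267 × 0.6 = 0.160, probability 0.1381
- maternal infection only: 0.267 × 3 = 0.801, probability 0.4447
- both: 0.267 × 1.8 = 0.481, probability 0.3246

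Among infected infants the maternal–eczema odds ratio becomes 0.619 × (0.3246 × 0.2107)/(0.4447 × 0.1381) = 0.619 × 1.114 = 0.69. Uninfected infants give the same value.

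If instead eczema raises later infection (odds ratio 1.67), the four probabilities are 0.1658, 0.2493, 0.3736 and 0.4990. The result is 0.619 × (0.4990 × 0.1658)/(0.3736 × 0.2493) = 0.55.

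*Other assumed structures*, from logistic models fitted to expected cell frequencies:

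| Structure | Without infant infection | With infant infection |
|---|---|---|
| Infant infection a mediator; direct OR 0.70; maternal–infant OR 1.5 to 4; infant–eczema OR 0.8 to 0.5 | 0.69 to 0.59 (total effect) | 0.70 |
| Unmeasured common cause of infant infection and eczema (OR 1.5 to 3 each); maternal–infant OR 2 to 3 | 0.62 to 0.64 | 0.60 to 0.68 |
| Shared household cause only (OR 3 to 4); no maternal-to-infant effect; infant–eczema OR 0.5 to 0.6; true OR 0.70 to 0.71 | 0.66 to 0.68 | 0.70 |
| Eczema first, as above, but maternal–infant OR 1 | 0.62 | 0.62 |

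Adjustment can therefore move the estimate toward the null, away from it, or not at all, and it can also remove bias.

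**4. Rough effect on power.** With 30% overall prevalence, an odds ratio of 0.70 corresponds to 26.3% vs 33.7%. Then z = (0.0746 − 0.05504)/0.0213 = 0.92, and power at alpha 0.01 falls from 98% to about 82%.

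**The case against.** **Shared household causes.** If mother and infant are infected only because they share a home, infant infection lies on a back-door path and acts as a proxy confounder. The third row of the table shows adjustment helping. This stands. A reader might infer that the primary estimate is simply biased, but the documents do not support that, because they do not give the maternal–infant or infant–eczema associations that would decide it.

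**Direct effect.** The two infections are separate primary exposures, so separating intrauterine from postnatal effects is a recognisable aim, and the article does not say that the total effect is wanted. This stands in part. A direct-effect analysis still needs infant infection to come before eczema, and a single any-to-24-months indicator does not ensure that.

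**Later cases.** The eczema discussion also says that prevalence peaks between 2 and 3 years, so some cases can follow infection. True, but the article still says that the reverse order is common.

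**Only an example.** The list is introduced as an example in a condensed article. That excuses what it leaves out, not what it puts in: it affirmatively labels infant infection an a priori confounder for a primary outcome.

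**Residence.** A reader might go on to infer that leaving out urban/rural residence biases the result toward protection. The article does say "Rural residence appears to be strongly protective against the development of allergic disease" and, of services, "in the rural areas, 10% have access to electricity and none have access to other services". But the first remark opens the asthma discussion, the list is illustrative, the eczema framework in Figure 5 is not shown, and no infection prevalence by area is given. Education and crowding could also absorb part of any such effect. Residence is a candidate covariate, not a demonstrated omission.

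**Conclusion.** The point holds in a limited form. The article's own timing shows that infant infection follows the exposure and often the eczema, so it should not be listed as an a priori confounder in the primary maternal–eczema model. The resulting odds ratio is not the total effect of maternal infection, nor a clean direct effect.

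How far the estimate would move is unknown. The range of 0.55 to 0.69 around a true 0.62 assumes a maternal–infant odds ratio of up to 3 and an eczema-to-infection odds ratio between 0.6 and 1.67. If either link is absent in that structure, nothing moves. The timing contradiction rests on the text alone; the magnitudes rest on assumptions.

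Nor is eczema shown to be the basis for policy on treatment in pregnancy. The article leaves interventions to future studies and asks for evidence from other settings.

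**What to change.** State which effect of maternal infection is wanted. Make the primary maternal–eczema model one that adjusts only for pre-exposure or baseline covariates: gender, maternal education, household crowding and other baseline household factors, with residence as a candidate. Move infant infection to a secondary, time-ordered analysis.

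Where infant infection is related to eczema, use a discrete-time or survival model with infection as a time-updated covariate. The existing stool visits (3, 7, 13, 18 and 24 months) and eczema assessments (7, 13, 24 and 36 months) allow this.

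Do not keep the logistic model and merely count infections before first eczema, because that shortens the exposure window in cases only. As an illustration with assumed inputs and no true effect, let infection reach 5% by 12 months, 17.5% by mid-second year and 30% by 24 months. Let eczema start before any infection in 60% of cases, around 12 months in 20%, in mid-second year in 10% and after 24 months in 10%. Exposure among cases is then 0.20 × 5% + 0.10 × 17.5% + 0.10 × 30% = 5.75%, against 30% in non-cases. The spurious odds ratio is (0.0575/0.9425)/(0.30/0.70) = 0.14.

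The cost is a change of wording in the analysis plan, with no new data collection. There are two drawbacks: the baseline covariates must carry the control of shared household causes, and the secondary analysis has fewer informative cases.
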